|           | 
Secondary objective 13 of this clinical investigation is to investigate the changes in fatigue after a 4-week RAGT as assessed by the Fatigue Severity Scale (FSS).
 
Secondary objective 14 of this clinical investigation is to explore the amount of individual and predefined goal achievement after a 4-week RAGT as assessed by Goal Attainment Scaling (GAS).
 
Secondary objective 15 of this clinical investigation is to explore the changes in gait parameters (gait speed, walking distance, number of steps and step length) over the RAGT intervention period as measured by the LEXO® robotic gait trainer.
 
Secondary objective 16 of this clinical investigation is to explore the changes in body weight and gait support (percentage of body weight support, percentage of active/passive gait modes) over the RAGT intervention period as measured by the LEXO® robotic gait trainer.
 
Secondary objective 17 of this clinical investigation is to develop a theory on the causal relationships between the RAGT and study outcomes with respect to the different study patient populations. This objective does not involve patient assessments.
 |
| Endpoints | 
Primary endpoint:
 
The primary endpoint of this clinical investigation is the feasibility of the methods and of a full-scale randomised controlled trial. This will be assessed by the recruitment, retention and adherence rates, a structured adverse events log, a Smiley Likert Scale asking four predefined questions on the acceptance of the intervention, as well as a semi-structured observation during the RAGT intervention for understanding the intervention context and process.
 
Secondary endpoints and assessments:
 
1.1 Number of falls– falls log [ambulatory patients]
 
1.2 Walking ability - Functional Ambulation Categories (FAC) [ambulatory patients]
 
1.3 Walking speed - 10-Metre Walk Test (10MWT) [ambulatory patients; assessed in clinical routine]
 
1.4 Dynamic balance during walking - Functional Gait Assessment (FGA) [ambulatory patients]
                                                                                                                                                                                                                                                          |

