The RAGT will be integrated into patients' inpatient rehabilitation and be planned at similar daytimes to reduce patient burden and facilitate comparability. The baseline and post-intervention examinations involve walking and balance tests and self-report questionnaires. This means that the patients may alternate between physical and mental activities, will be supported as required and as permissible with respect to the test instructions, and they may take a rest at any time. Therefore, the clinical investigation procedures are classified as low burdensome. Since the clinical investigation will be conducted in an inpatient rehabilitation environment, the participants will not be required to travel to the clinical investigation site.

With respect to the benefits from the RAGT, it is expected that the patients will improve their walking or gain walking ability (severely affected patients post stroke in the subacute phase). The results gained from this clinical investigation will help to optimise RAGT

protocols with respect to patients with different neurological diseases, which will contribute to better rehabilitation outcomes in the long-term. In summary, the expected benefits – treatment optimisation and more efficient and effective rehabilitation – outweigh the low-level risks and burden for patients, therefore the study procedures only represent a minor health risk and merely slight burden for patients, based on the current state of medical knowledge.

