### **2.3. Secondary objectives**

Secondary objective 1 of this clinical investigation is to investigate the changes in the fall-rate after a 4-week RAGT as assessed narratively by the number of falls in ambulatory patients.

Secondary objective 2 of this clinical investigation is to investigate the changes in walking ability after a 4-week RAGT as assessed by the Functional Ambulation Categories (FAC).

Secondary objective 3 of this clinical investigation is to investigate the changes in walking speed after a 4-week RAGT as assessed by the 10-Metre Walk Test (10MWT) in ambulatory patients.

Secondary objective 4 of this clinical investigation is to investigate the changes in dynamic balance after a 4-week RAGT during walking as assessed by the Functional Gait Assessment (FGA) in ambulatory patients.

Secondary objective 5 of this clinical investigation is to investigate the changes in walking distance after a 4-week RAGT as assessed by the 6-Minute Walk Test (6MWT) in ambulatory patients.

Secondary objective 6 of this clinical investigation is to investigate the changes in functional mobility after a 4-week RAGT as assessed by the Timed Up and Go test (TUG) in ambulatory patients.

Secondary objective 7 of this clinical investigation is to investigate the changes in dynamic balance after a 4-week RAGT as assessed by the Four-Square Step Test (FSST) in ambulatory patients.

Secondary objective 8 of this clinical investigation is to investigate the changes in trunk movement after a 4-week RAGT as assessed by the Trunk Control Test (TCT) in non-ambulatory patients.

Secondary objective 9 of this clinical investigation is to investigate the changes in the limits of stability with respect to trunk movements after a 4-week RAGT as assessed by the Modified Functional Reach Test (MFRT) in non-ambulatory patients.

Secondary objective 10 of this clinical investigation is to investigate the changes in fall-related self-efficacy after a 4-week RAGT as assessed by the Falls Efficacy Scale- International Version (FES-I).

Secondary objective 11 of this clinical investigation is to investigate the changes in health-related quality of life (HRQoL) after a 4-week RAGT as assessed by the 5-level EQ-5D version (EQ-5D-5L).

Secondary objective 12 of this clinical investigation is to investigate the changes in depression after a 4-week RAGT as assessed by the Beck Depression Inventory, second edition (BDI-II).

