**Secondary endpoints**

The secondary endpoints for this clinical investigation and how they will be assessed are presented in Table 7. The validated German version of all assessments will be used, which have demonstrated good to excellent properties. In addition, the collection timepoints are shown. The assessments which will be ***performed in clinical routine are highlighted in green***, with the remaining assessments being ***performed as part of the clinical investigation (highlighted yellow)***.

**Table 7:** Secondary endpoints and assessment

| No. | Secondary endpoint | Assessment                                                   | Scr | BL  | PI | IV |
|-----|--------------------|--------------------------------------------------------------|-----|-----|----|----|
| 1.1 | Number of falls    | Falls log [ambulatory patients] (see CRF)                    |     | x   | x  |    |
| 1.2 | Walking ability    | Functional Ambulation Categories (FAC) [ambulatory patients] | x   | (c) | x  |    |

|      |                                                                                                           |                                                                                       |    |   |    |   |
|------|-----------------------------------------------------------------------------------------------------------|---------------------------------------------------------------------------------------|----|---|----|---|
| 1.3  | Walking speed                                                                                             | 10-Metre Walk Test (10MWT)
[ambulatory patients, assessed in clinical routine]     |    | x | x  |   |
| 1.4  | Dynamic balance during walking                                                                            | Functional Gait Assessment (FGA)
[ambulatory patients]                             |    | x | x  |   |
| 1.5  | Walking distance                                                                                          | 6-Minute Walk Test (6MWT)
[ambulatory patients, assessed in clinical routine]      |    | x | x  |   |
| 1.6  | Functional mobility                                                                                       | Timed Up and Go test (TUG)
[ambulatory patients]                                   |    | x | x  |   |

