The Timed-Up and Go (TUG) will be used to measure functional mobility (Podsiadlo and Richardson, 1991). The TUG can be used as an indicator of the risk of falling during everyday movement tasks. The activities tested are transferring from sitting to standing, walking, turning around in space, going back to the chair and sitting down. For everyday locomotion and reducing the risk of falling, the skills of transferring from sitting to standing and turning in space are of crucial importance (Cheng et al., 1998; Mong et al., 2010). The test begins in the seat, on a chair with a seat height of approx. 46 cm. For the implementation of the TUG, the time that the patient needs to get up from the chair, walk a distance of three meters, turn around, go back three meters to the chair and get back into it, is stopped to move to the starting position. The time required is documented in seconds. Walking aids may be used. All aids used must be documented. The TUG takes less than 5 minutes to complete.

The Four Step Square Test (FSST) (Dite and Temple, 2002) assesses balance and the ability to climb over obstacles forwards, sideways and backwards. The patients stand in a square created by a marked test cross on the floor (see CRF). The patients are asked to step clockwise and then counterclockwise into all four squares. To do this, they have to step forward, to the side and backwards over the marked test cross. There are always two runs, a test run and a run in which the time is stopped. The implementation time is less than 5 minutes.

The Trunk Control Test (TCT) (Franchignoni et al., 1997) will be used in its German version (Fischer, 2014) to assess trunk mobility in severely affected, non-ambulatory stroke patients in the subacute stage. The TCT assesses four movement activities: rolling from a supine position to the weak side (1) and to the strong side (2), sitting up from a lying-down position (3), and sitting balance (4). The scoring is as follows: 0, unable to perform movement

without assistance; 12, able to perform movement but in an abnormal manner; and 25, able to complete movement normally. The TCT score is the sum of the scores obtained on the four tests (range, 0 to 100) (Franchignoni et al., 1997; Hsieh et al., 2002).

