*injury assessment: assessment and imaging for spinal injury. NICE Guideline NG41, 2016*), valid at the time of diagnosis, with spinal cord injury (SCI), the Ataxia Medical Guidelines 2016 or earlier versions, developed by Ataxia UK, London (de Silva et al., 2019) with hereditary ataxias, the diagnostic criteria originally developed by the National Institute of Neurological Disorders and Stroke (NINDS) ("Criteria for diagnosis of Guillain-Barré syndrome," 1978) in its revised version (Asbury & Cornblath, 1990; Hadden et al., 1998; Uncini et al., 2010) with GBS, the diagnostic criteria of the European Federation of Neurological Societies/Peripheral Nerve Society Guideline on the management of chronic inflammatory demyelinating polyradiculoneuropathy- First Revision ("European Federation of Neurological Societies/Peripheral Nerve Society Guideline on management of chronic inflammatory demyelinating polyradiculoneuropathy: report of a joint task force of the European Federation of Neurological Societies and the Peripheral Nerve Society--First Revision," 2010) or earlier versions with chronic inflammatory demyelinating polyneuropathy (CIDP) and the diagnostic criteria for ALS from the World Federation of Neurology as the El Escorial Criteria (Brooks, 1994), in their revised version as the Airlie House criteria (or El Escorial revised) (Brooks et al., 2000) or Awaji criteria (de Carvalho et al., 2008), or the recently developed Gold Coast criteria (Johnsen, 2020). There are no formal criteria for progressive muscular atrophy (PMA) and primary lateral sclerosis (PLS).

Patients with subacute, severe stroke who are non-ambulatory are eligible if they can be verticalised for at least 1 hour twice a day (which is a requirement for inpatient rehabilitation at the Reha Zentrum Münster). Patients with motor neuron disease in the early, active stage of the disease will be included and patients with mild to moderate hereditary ataxia. Patients will only be included if they are able to participate in this clinical investigation over its complete duration, which will be evaluated by the study PI. Further inclusion criteria will be impairment in walking according to the neurological exam assessed by a neurologist and Functional Ambulation Categories (FAC) of 0-4, intact cognitive function as defined by a score of  $\geq 24/30$  points on the Mini Mental State Examination (MMSE) (Folstein et al., 1975).

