The first phase of the analysis will involve a descriptive analysis for all disease groups using the mean (SD) or median (range, 25th and 75th percentiles). The second phase of the analysis will include inferential statistics using a pre-post analysis of the data from the total sample (one group). For continuous data, a paired t-test will be performed and for ordinal data, a Wilcoxon Signed Rank test.

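### Endpoint 1.2 limits FAC to ambulatory patients, against objective 2 and the entry range, so a change from not walking to walking would not be analysed

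*Protocol*

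**What the plan says.** **FAC as an endpoint.** The synopsis lists "1.2 Walking ability - Functional Ambulation Categories (FAC) [ambulatory patients", and Table 7 in section 4.8 repeats the restriction at row 1.2: "Functional Ambulation Categories (FAC) [ambulatory patients". The same row marks FAC at screening, carries that score to baseline, and marks FAC again post-intervention.

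**FAC as an objective.** Secondary objective 2 in section 2.3 is "to investigate the changes in walking ability after a 4-week RAGT as assessed by the Functional Ambulation Categories (FAC". It names no subgroup, whereas objectives 1 and 3 to 7 are each confined to ambulatory patients. The description of FAC in section 4.8 gives it two uses, screening and post-intervention rating of walking ability, again without a subgroup.

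**Who enters and what is expected.** Section 5.4 admits "Functional Ambulation Categories (FAC) of 0-4" and allows non-ambulatory patients with severe subacute stroke. Section 1.3 states: "it is expected that the patients will improve their walking or gain walking ability (severely affected patients post stroke in the subacute phase".

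**Trunk tests.** Objectives 8 and 9 and Table 7 give TCT and MFRT to non-ambulatory patients with no diagnosis named. The assessment text in section 4.8 narrows both; for TCT the purpose is "to assess trunk mobility in severely affected, non-ambulatory stroke patients in the subacute stage".

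**Analysis.** Section 8.2 applies the tests to the total sample at two-sided 0.05: "For continuous data, a paired t-test will be performed and for ordinal data, a Wilcoxon Signed Rank test". FAC and TCT are listed as ordinal and MFRT as continuous.

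**The concern.** The benefit named for the most severely affected stratum is a transition from not walking to walking. Under the endpoint definition, a patient who is non-ambulatory at baseline is outside the FAC analysis, so that transition would be left out even though the baseline score is already on file.

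The study's stated purposes include preliminary effects, and its results are meant to inform a randomised trial. An FAC result drawn only from patients who already walked would say nothing about the group in which section 1.3 reports the largest benefit in the stroke literature, namely those unable to walk. A T2 rating that was never taken cannot be recovered after discharge.

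The trunk-test populations raise a related question. Depending on which text governs, the TCT hypothesis may be tested on so few pairs that the outcome depends on which version of the test the software runs.

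**Working it through.** **1. Planned numbers.** Section 5.3 gives four strata of 5 and four of 2: 4 × 5 + 4 × 2 = 28, which reproduces the stated total. Severe subacute stroke is one of the strata of 5. Attrition is put at 10% without replacement: 28 × 0.9 = 25.2 patients overall and 5 × 0.9 = 4.5 in that stratum.

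**2. FAC population, place by place.**

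| Place | Limited to ambulatory patients? |
|---|---|
| Synopsis, endpoint 1.2 | Yes |
| Table 7, row 1.2 | Yes |
| Synopsis and section 2.3, objective 2 | No |
| Section 4.8, description of FAC | No |
| Table 5 and section 5.4, entry FAC 0–4 | No, includes FAC 0 |
| Section 2.4, functional ambulation in the null hypothesis | No |

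Two places carry the restriction. The objective, the assessment text, the entry rule and the null hypothesis do not.

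**3. Does another planned test capture the transition?** The other walking and balance tests (10MWT, FGA, 6MWT, TUG, FSST) are all limited to ambulatory patients. The 10MWT is walked without assistance and the 6MWT without physical help. FAC grades how much human support is needed, so it alone can register a move from unable to walk to walking with help. The LEXO gait measures apply to everyone, but they are taken on the device with adjustable speed and body weight support and do not measure overground walking.

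**4. How many patients.** In the subacute stroke stratum the number excluded lies between 0 and 5, because non-ambulatory status is allowed there but not required. Other strata could add to it, since FAC 0–4 is the entry rule for all. If all 5 are non-ambulatory and nobody else is, the FAC analysis has at most 28 − 5 = 23 pairs instead of 28. With the restriction removed it has up to 28, or about 25 after the expected attrition.

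**5. TCT by exact signed-rank test.** The smallest two-sided p with n non-zero pairs is 2/2^n:
- n = 4: 2/16 = 0.125
- n = 5: 2/32 = 0.0625
- n = 6: 2/64 = 0.031

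With 5 pairs all improving and no ties, the normal approximation gives z = 7.5/√13.75 = 2.02, p = 0.043 without continuity correction, and p = 0.059 with it. Under independent 10% attrition (an assumption), the chance that all 5 stay is 0.9^5 = 0.59.

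**6. MFRT by paired t-test.** Significance needs mean change divided by SD of change above t(0.975, n−1)/√n: 2.776/√5 = 1.24 at n = 5 and 3.182/√4 = 1.59 at n = 4. A significant result is possible, though only for a large change.

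**The case against.** The strongest reply is that this is a drafting conflict and not a decision to exclude anyone. The objective, the assessment text and the carry-over of the screening score all read naturally as FAC in everyone, and the team may well have rated it that way. This reply stands as to intent. It does not remove the need for correction, because Table 7 is the operative list of what is assessed, in whom and when.

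A second reply is that these patients are still measured. FES-I, EQ-5D-5L, BDI-II, goal attainment and the LEXO measures apply to them, and the training is observed in weeks 1 and 4. This is correct. A reader might infer that the group loses its only walking-related outcome, and the protocol does not support that. What is missing is a measure of overground walking that allows for human help.

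A third reply is that feasibility is primary, no formal sample size was calculated, and the limitations already rule out efficacy tests by disease group. That lowers the stakes but does not settle which patients the FAC result describes.

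On the trunk tests, a reader might infer that the trunk hypotheses can never be rejected. The documents do not support this. MFRT gets a t-test; the protocol does not say whether the Wilcoxon test is exact, a detail commonly left to the SAP; and Table 7 would allow more than 5 pairs if other strata enrol non-ambulatory patients.

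**Conclusion.** The inconsistency is real and should be corrected. Followed literally, endpoint 1.2 leaves out the change that the risk-benefit section expects in severe subacute stroke, and no other planned overground test records it.

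The size is up to 5 patients in that stratum plus any non-ambulatory patients elsewhere. A fixed share such as 5/28 = 18% should not be inferred, because non-ambulatory status is not required and the text gives no FAC cut-off for ambulatory. The conclusion assumes that Table 7 governs conduct and that FAC 0 counts as non-ambulatory.

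The secondary point is narrower. The TCT and MFRT population is stated in two ways. If it is the subacute stroke stratum, with at most 5 pairs, an exact test of TCT has a floor of p = 0.0625. That limit belongs to TCT and the exact version only.

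Nor do the documents call for entering zeros on the 10MWT or 6MWT for patients who cannot walk. As the 10MWT is walked without assistance, a zero would merge patients who walk with help and patients who cannot walk, and it would redefine both endpoints.

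**What to change.** 1. Delete the ambulatory restriction at endpoint 1.2 in both the synopsis and Table 7, so that it agrees with objective 2.
2. Rate FAC at T2 in all participants, and include everyone with both ratings in the pre-post Wilcoxon test.
3. Choose one population for TCT and MFRT, and use it in objectives 8 and 9, the synopsis, Table 7 and the assessment text. If it is the subacute stroke stratum, report TCT as individual values and median change without a significance test. The paired t-test for MFRT can stay, with its small n made plain.

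The cost is an amendment to a few lines and one short visual rating in a few patients at a visit they already attend. Baseline values exist from screening, and no new instrument or test is needed.

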Secondary objective 13 of this clinical investigation is to investigate the changes in fatigue after a 4-week RAGT as assessed by the Fatigue Severity Scale (FSS).

Secondary objective 14 of this clinical investigation is to explore the amount of individual and predefined goal achievement after a 4-week RAGT as assessed by Goal Attainment Scaling (GAS).

Secondary objective 15 of this clinical investigation is to explore the changes in gait parameters (gait speed, walking distance, number of steps and step length) over the RAGT intervention period as measured by the LEXO® robotic gait trainer.

Secondary objective 16 of this clinical investigation is to explore the changes in body weight and gait support (percentage of body weight support, percentage of active/passive gait modes) over the RAGT intervention period as measured by the LEXO® robotic gait trainer.

Secondary objective 17 of this clinical investigation is to develop a theory on the causal relationships between the RAGT and study outcomes with respect to the different study patient populations. This objective does not involve patient assessments.

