## 4.5 Data collection

After eligibility screening, a screening for cognitive impairment (Scr) will be performed. In eligible patients who pass the cognitive screening, study specific assessment data will be collected at baseline (T1) and post-intervention (T2) at 4 weeks after completion. Assessments will be performed at similar daytimes to increase comparability. Information on demographic and disease specific patient characteristics will be extracted from patients' charts. Further disease-specific data will be collected by neurologists (PI, investigator), cognitive screening will be performed by psychologists as part of the clinical routine, and movement and function-related data will be collected by trained physiotherapists. The study participants will be

supported as required and as permissible with respect to the test instructions, and they may take a rest at any time.

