| 1.7  | Dynamic balance                                                                                           | Four-Square Step Test (FSST)
[ambulatory patients]                                 |    | x | x  |   |
| 1.8  | Trunk movement                                                                                            | Trunk Control Test (TCT) [non-ambulatory patients]                                    |    | x | x  |   |
| 1.9  | Limits of stability with respect to trunk movements                                                       | Modified Functional Reach Test (MFRT) [non-ambulatory patients]                       |    | x | x  |   |
| 1.10 | Fall-related self-efficacy                                                                                | Falls Efficacy Scale- International Version (FES-I)                                   |    | x | x  |   |
| 1.11 | Health-related quality of life                                                                            | 5-level EQ-5D version (EQ-5D-5L)                                                      |    | x | x  |   |
| 1.12 | Depression                                                                                                | Beck Depression Inventory, second edition (BDI-II)                                    |    | x | x  |   |
| 1.13 | Fatigue                                                                                                   | Fatigue Severity Scale (FSS)                                                          |    |   | x  |   |
| 1.14 | Goal definition and evaluation of its achievement                                                         | SMART defined movement-related individual goal (a); Goal Attainment Scaling (GAS) (b) | ax |   | bx |   |
| 1.15 | Gait parameters (gait speed, walking distance, number of steps and step length)                           | Measured by LEXO® during the intervention as part of the clinical routine             |    |   |    | x |
| 1.16 | Body weight and gait support (percentage of body weight support, percentage of active/passive gait modes) | Measured by LEXO® during the intervention as part of the clinical routine             |    |   |    | x |

Abbreviation: Scr=screening; SMART=specific, measurable, attractive, realistic and terminated; c=data carryover to baseline if patient has passed the screening; BL=baseline; PI=post-intervention; IV=intervention period (at all intervention sessions)

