### ***Limitations***

- Low number of patients per diagnosis – due to low power, efficacy testing cannot be performed for the different disease groups but overall.
- Limited generalizability of results
- No control group
- No follow-up assessment

As outlined in Chapter 2.1, the purpose of this clinical investigation is to investigate the feasibility and acceptability and compare the preliminary effects of RAGT a mixed population with neurological diseases consisting of patients with stroke in the subacute and chronic phases and with severe and mild to moderate disability, MS, Parkinson's Disease, spastic para-or tetraplegia, mild to medium grade hereditary ataxia, acute or chronic inflammatory demyelinating polyneuropathy and motoneuron disease. A further purpose of this clinical investigation is to synthesise quantitative and qualitative results for examining causality i.e., the extent to which the RAGT intervention may have caused the outcomes.

The results from this study can be used for designing a full-scale randomised controlled trial. The study population and all study procedures have been specified a priori, the study team will strive to carry out all measures as planned and use a structured data documentation, management and evaluation as outlined in this clinical investigation protocol. The intervention of this study uses a standard RAGT protocol but is individualised and hence adapted to the different patient groups (Cases 1-8) and the individual performance level of the participants. Continuous monitoring for adverse events using a structured log and predefined evaluation criteria will be performed. Therefore, it is not expected that the limitations of this study negatively impact on the conduct of the clinical investigation, data quality and results.

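### The fatigue scale (FSS) is scheduled only after the intervention, so its planned pre-post change cannot be computed; the timing of T2 is also contradictory

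*Protocol*

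**What the plan says.** **Fatigue.** Section 2.3, objective 13, is "to investigate the changes in fatigue after a 4-week RAGT as assessed by the Fatigue Severity Scale (FSS"). The null hypothesis in 2.4 lists fatigue among the outcomes that do not change. Section 8.2 (Planned statistical analysis) classes the FSS as ordinal and states: "The second phase of the analysis will include inferential statistics using a pre-post analysis of the data from the total sample". Ordinal outcomes are assigned the Wilcoxon signed-rank test.

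Section 4.8 refers the reader to Table 7 for the collection times, with the key "BL=baseline; PI=post-intervention; IV=intervention period (at all intervention sessions"). Row 1.13, "Fatigue Severity Scale (FSS"), has a mark under post-intervention and none under screening or baseline.

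**Timing of T2.** Section 4.5 says that study data are collected at baseline and "post-intervention (T2) at 4 weeks after completion". Section 5.2 describes the span from baseline to post-intervention testing as four weeks. Table 8 in 7.1 places T2 after 4 weeks. Section 5.6 counts both assessments and the intervention within a four-week period, and sets last patient in at 31.3.2023 and last patient out at 30.4.2023. The limitations include "No follow-up assessment".

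**The concern.** A change score and a signed-rank test both need two FSS values per patient. The printed schedule provides one. The study has no control group, so the patient's own baseline is the only comparator. A single score after training cannot separate fatigue that was already present, as is likely in these diagnoses, from fatigue that changed over the four weeks. Training starts within a day or two of inclusion, so the chance to collect the baseline is short and does not come back.

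The T2 contradiction is a separate defect, and it touches every pre-post outcome. If a site followed 4.5 literally, each change would describe the patient about four weeks after training stopped rather than at its end. The result would then mix any training effect with whatever happened afterwards.

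**Working it through.** **1. FSS schedule against its neighbours (Table 7)**

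| Row | Instrument | Screening | Baseline | Post |
|---|---|---|---|---|
| 1.2 | FAC | marked | carried over (c) | marked |
| 1.10 | FES-I | – | marked | marked |
| 1.11 | EQ-5D-5L | – | marked | marked |
| 1.12 | BDI-II | – | marked | marked |
| 1.13 | FSS | – | – | marked |
| 1.14 | GAS | goal set | – | goal scored |

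Two rows lack an ordinary baseline mark for a stated or evident reason. The FAC uses its screening value, under the note "c=data carryover to baseline if patient has passed the screening". The GAS is a goal set in advance and scored once at the end. Neither reason applies to the FSS: it has no screening value to carry over, and it is a state measure that needs two readings.

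**2. Number of analysable pairs**

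The signed-rank test works on the differences dᵢ = FSS(T2)ᵢ − FSS(T1)ᵢ, so a patient counts only if both values exist.

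- Total sample (section 5.3): four groups of 5 and four groups of 2, so 4 × 5 + 4 × 2 = 28. This agrees with the protocol.
- Table 7 as printed: T1 is not collected, so there are 0 pairs of 28.
- With a baseline FSS: up to 28 pairs. At the 10% attrition expected in 5.3, 28 × 0.90 = 25.2, so about 25.

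**3. Timing of T2**

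Inputs: last patient in 31.3.2023 and last patient out 30.4.2023 (5.6; a stray 2022 after the first date is ignored), and four weeks of training counted as 28 days. Table 8 starts training on day 1–2 after inclusion; day 0 is included here as the most favourable case.

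The protocol's own window is 31.3.2023 to 30.4.2023 = 30 days.

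| Training starts on day | T2 at end of training | Against 30.4.2023 | T2 four weeks later | Against 30.4.2023 |
|---|---|---|---|---|
| 0 | 28.4.2023 (28 days) | 2 days before | 26.5.2023 (56 days) | 26 days after |
| 1 | 29.4.2023 (29 days) | 1 day before | 27.5.2023 (57 days) | 27 days after |
| 2 | 30.4.2023 (30 days) | same day | 28.5.2023 (58 days) | 28 days after |

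T2 at the end of training reproduces the planned last visit. The literal reading of 4.5 needs 28 + 28 = 56 days at the least and cannot fit.

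**The case against.** The strongest reply is that the blank cell is a typing omission that the rest of the protocol corrects. Section 1.3 and the German summary say that questionnaires are given at both visits. Section 4.5 says that study assessments are taken at T1 and T2 without exempting the FSS. Table 8 allots the same time to both visits. A reader of objective 13 would expect a baseline. The CRF, which staff actually fill in, is not part of the document and may already contain it. The marks in this part of the table may also be loose: goal setting in row 1.14 sits under screening, while Table 8 puts it at day 0–1 after inclusion.

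Much of this is fair. The gap is probably unintended, and 0 of 28 is what happens if Table 7 is followed as printed, not a forecast. A mark lost when the text was extracted cannot be fully ruled out, although the post-intervention mark in the same row and the baseline marks in the three rows above came through. What the reply does not supply is any place that names a baseline FSS. Section 10.6 limits the CRF to data listed in the protocol, so an omission here can carry through to collection.

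Two further points stand. Fatigue as a side effect is also captured by the adverse-event log and by the observations in weeks 1 and 4, so safety monitoring does not depend on the FSS. The FSS is one of 16 secondary endpoints, so no feasibility criterion changes.

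On T2, the sentence in 4.5 may be a garbled reference to completing the four weeks, and every other section disagrees with it. That makes the correction easy to choose, but the sentence stands in the section that governs data collection.

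**Conclusion.** Both parts hold. Under the printed schedule a named hypothesis, no change in fatigue, cannot be tested: there are 0 of 28 FSS pairs, against about 25 to 28 if a baseline is taken. The loss would be permanent for each patient who starts training without it. This rests on Table 7 being read as printed and followed.

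The T2 wording in 4.5 conflicts with 5.2, 5.6, Table 8 and the limitation of no follow-up. It would overrun the planned last visit by 26 to 28 days, assuming that the last patient enters on 31.3.2023 and that training starts within two days. Only the end-of-training reading is consistent with the protocol's dates.

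The consequence is confined to secondary endpoints. Correction before the first patient is enrolled is still warranted, because the missing measurement cannot be obtained later.

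**What to change.** 1. In Table 7, row 1.13, add a mark in the baseline column. Check that the CRF has the FSS at baseline as well as post-intervention, and add it if it does not.
2. In section 4.5, reword the timing of T2 so that it falls at the end of the 4-week intervention, in line with 5.2, 5.6, Table 8 and the limitations.

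The cost is one nine-item questionnaire at a baseline visit already planned at 70–90 minutes beyond routine, plus one corrected sentence. The sample size, the planned analysis and the timeline do not change.
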